## Abstract

**Background:**

Falls in hospitals remain a major challenge to patient safety. All hospitalised adults are at risk of falling during their inpatient stay, though this risk is not always realised by patients and clinicians. This study will evaluate the outcomes of a hospital clinician education program that teaches clinicians how to screen for falls risk and assign mitigation strategies using clinical reasoning, rather than relying on a standardised falls risk assessment tool (FRAT). The education program aims to increase clinician knowledge, motivation and confidence in screening falls risk and selecting individual falls prevention interventions. Perceptions of the education intervention will also be examined.

**Methods:**

Participants will be a sample of convenience of nurses and allied health professionals from five Australian hospitals. For each hospital there will be two cohorts. Cohort 1 will be clinical leaders who shall receive a three-hour education program on the latest evidence in hospital falls risk assessment and how to implement a new falls screening and management tool. They will also be taught practical skills to enable them to deliver an effective one-hour in-service training session to Cohort 2. Cohort 2 will be recruited from the workforce as a whole and include nurses and other health professionals involved in routine hospital falls screening and prevention.

The investigation will be framed on Keller’s Model of Motivational Design and Kirkpatrick’s evaluation framework. It will involve a mixed methods pre and post-test questionnaire design inclusive of semi-structured telephone interviews, to triangulate the data from multiple approaches.

**Discussion:**

This study will quantify the outcomes of a high-quality clinician education program to increase knowledge of evidence-based practice for falls prevention. It is predicted that positive behavioural changes will occur in health professionals, leading to organisational change and improved patient outcomes. Furthermore, the findings from the study will inform the future refinement of educational delivery to health professionals across hospital sites.

**Trial registration:**

The study has also been approved by the Australian New Zealand Clinical Trials Registry: Preventing Hospital Falls: Optimal Screening UTN U1111-1225-8450.

**Universal Trial Number (UTN):** U1111–1228-0041 (obtained 5/2/19).

**Australian New Zealand Clinical Trials Registry (ANZCTR):** ACTRN12619000200189 (obtained 12/2/19).

## Background

Falls remain a serious problem in private and public hospitals world-wide and are associated with marked morbidity, mortality, increased length of stay and re-admissions [1–5]. Falls also incur substantial costs to hospitals and healthcare providers, insurers and individuals [6–8]. Whilst international estimates on falls are hard to find due to differences in reporting between countries, in the United Kingdom, the Royal College of Physicians’ National Audit of Inpatient Falls reported an average of 6.63 falls per 1000 occupied bed days [9].

This study is directed towards evaluating a clinician education program on how to screen hospital falls risk and assign mitigation strategies using clinical reasoning, rather than relying on a standardised Falls Risk Assessment Tool (FRAT). Historically, FRATs were used to try and identify patients at risk of falling whilst in hospital [10, 11]. As well as having poor predictive validity, it is now recognised that all hospitalised adults are at risk of falling during an episode of care [12]. The National Institute for Health and Care Excellence (NICE) guidelines state that, ‘fall risk prediction tools should not be used to predict inpatients’ risk of falling in hospital’ [13]. Furthermore, they advise that, ‘all patients aged 65 years or older and patients aged 50 to 64 years who are judged by a clinician to be at higher risk of falling due to an underlying condition, should be judged as being at risk of falling and their care managed according to recommendations' [13].

Research into the impact of education interventions on falls within hospitals has mainly focussed on patient education [14] and many interventions fail to adequately describe the educational methods employed [15]. As a precursor to this study, a scoping review was performed to determine the extent of the research evidence and design elements, for education interventions for health professionals in falls screening and prevention. There were few studies on this topic. One study described the outcomes of a half day education programme about fall and fracture prevention for staff given by specialist osteoporosis nurses in care facilities [16]. It did not find evidence for a reduction in the rate of falls [16] and the quality of evidence was assessed in a recent Cochrane review as being very low [17]. A pilot cluster-randomised trial in residential aged care evaluated an educational programme to improve staff connections, communication, and problem solving for the implementation of a falls quality improvement programme [18]. This trial of 546 eligible clinicians in four intervention nursing homes, did not find a change in falls rates. Notably, few education studies discussed in depth the educational approaches used, or whether theoretical principles were incorporated into their design [19].

The aims of the current study are to: (i) Investigate the self-reported views of hospital clinicians of their knowledge, clinical practice, confidence, motivation and attitudes towards screening for falls risk using traditional and contemporary approaches; (ii) Examine perceptions of an education intervention designed to communicate the latest evidence on falls screening and how to implement a new evidence-based Falls Screening Tool into daily clinical practice; (iii) Determine the effectiveness of the educational program content and delivery in supporting behaviour change for falls screening in hospitals. We shall also explore the views and experiences of health professionals on hospital falls risk screening and historical FRATs more generally.

## Methods/ design

### Design

This study is part of a large National Health and Medical Research Council of Australia partnership grant program of work, on falls prevention in hospitals ([name] et al., GNT1152853). For the larger trial, ten Australian hospitals will be randomised to an intervention group (five hospitals using a new Falls Screening Tool), or a control group (five hospitals continuing to use the historical FRAT form) by another organisation (The University of Melbourne). The new Falls Screening Tool removes the risk assessment component from the historical FRAT form and associated summary scores, yet maintains other components for falls mitigation. This education trial will be conducted at the 5 intervention hospitals.

### Participants and recruitment methods

At each of the intervention hospitals, there will be two separate cohorts. The names and contact details of all potential participants will be obtained from an existing hospital database.

*Cohort 1*: (*n* = 10 clinical leaders at each experimental hospital), will be approached by the Hospital General Manager to consider participating in the study. These clinical leaders will be invited to participate via email, which will contain all details about the study, the requirements for participation, and the Participant Information and Consent Form (PICF) (Additional file 1). On the day of the education, cohort 1 will be required to complete the written PICF, Pre-test and Post-test 1 surveys and return them to the researcher who is leading the education program. The PICF will also include consent to participate in a follow up telephone interview. Only those providing their contact details and consent will be contacted to participate in the interviews. Completing the Post-test 2 survey online will imply consent.

*Cohort 2:* (*n =* All nurses and allied health professionals involved in completing falls screening), will be eligible to participate and will be invited to attend a one-hour in-service education program. Staff will be asked to read the PICF (Additional file 2), which outlines the full details of the research project and the requirements for participation. Participants will be drawn from all wards in the five intervention hospitals, excluding paediatric, maternity, emergency and theatre wards. We are aiming for 65% attendance of all nurses and allied health professionals at each experimental site. On the day of the in-service training, cohort 2 will be required to complete the written PICF, Pre-test and Post-test 1 surveys. These will then be returned to the researchers via registered post. The PICF will also include consent to participate in a follow up telephone interview. Only those providing their contact details and consent will be contacted to participate in the interviews. Completing the Post-test 2 survey online will imply consent.

#### Intervention

The theoretical concepts and principles underpinning the educational intervention design and research methods of the study are based on behavioural and social sciences theory. Keller’s motivational design for learning and performance will be incorporated into the instructional design and research measurement outcomes. For the education protocol, participants will receive a high-quality education program on evidence-based hospital falls screening underpinned by quality education design principles put forward by Kiegaldie and Farlie [15]. The education intervention aims to increase participant knowledge, motivation and confidence about evidence-based practice on the use of a new falls screening tool that focusses on clinical reasoning and patient-centred, personalised falls prevention programs. The educational program also aims to support effective implementation of the new learnings into clinical practice. In order to implement this new intervention, a multifaceted educational approach will be employed that utilises a mixture of interactive teaching methods suited to the learning needs of busy clinicians [20].

The new Falls Screening Tool aims to enable clinicians to screen hospital patients, and assign appropriate falls mitigation interventions. The screening items identify, for example, whether or not the person is hospitalised, those aged 65 years or older, those who have had a fall in the past 12 months, anyone with sight, hearing or sensory deficits, and anyone who has received an anaesthetic in the last 24 h. The screening tool provides an opportunity for clinicians to use their judgement to determine the appropriate falls prevention interventions that are listed in a separate section on the form.

### Education intervention

#### Cohort 1

Will receive a three-hour education program using best educational design [15], which will educate clinical leaders on the latest evidence on hospital falls risk assessment and guide them in how to implement a new Falls Screening Tool. Teaching methods will include: content delivery on the latest evidence for falls screening; interactive face-to-face teaching; small group critical thinking activities on the challenges of falls prevention in hospitals, and the arguments for and against the use of FRATs; practical exercises using clinical vignettes to compare and contrast the historical FRAT and the new Falls Screening Too; and feedback gauging their views on each of the forms. Participants in cohort 1 will also be provided with the practical skills and associated educational resources, to enable them to deliver an effective, one-hour in-service training session on these topics, to cohort 2.

#### Cohort 2

Will attend a one-hour in-service training and be educated by cohort 1. Methods of educational delivery will also include: interactive face-to face teaching; content delivery on the latest evidence for falls risk assessment; small group critical thinking activities; and practical exercises using clinical vignettes (Fig. 1).

**Fig. 1 Fig1:**
[figure not shown]
Study protocol for the Parent Trial. This sub study pertains to clinician education used for the intervention group

### Data collection

A Pre and Post-test design will be used, elaborated through a mixed methods research approach, with the qualitative data helping to build on the initial quantitative results [21]. Data will be collected via de-identified surveys (using the participants’ initials and last three digits of their mobile telephone number) and individual telephone interviews. Multiple time points will be used for data collection from surveys:

(1) Pre-test: Immediately prior to the education program.

(2) Post-test 1: Immediately post the education program.

(3) Post-test 2: 2 months post implementation of the new screening tool.

For cohort 1, paper-based surveys will be collected by those who deliver the education program. For cohort 2, all surveys will be returned to researchers via registered post.

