### Strengths and limitations

This study is unique and the educational program can be delivered in a busy, time pressured clinical environment using clinical champions (leaders) and a ‘train the trainer’ approach. We shall clearly report the educational features so that others can adopt a best practice approach to educational design. The education interventions are designed to be readily implemented across other hospital sites and applied to other clinical education interventions. This study is not without limitations. There is a time factor related to educating Cohort 2, and education on a new clinical form may not be seen as a high priority for clinicians in a busy clinical environment with competing demands on time. There is also the potential for inaccurate self-reporting caused by recall bias [30] influenced by different clinicians’ perceptions. Loss to follow up is also likely, particularly for post survey 2 when moving from paper based surveys to online surveys.

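### Cohort 1 returns its coded Pre-test and Post-test 1 surveys to the person who taught the session, which can bias the Post-test 1 answers

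*Protocol article*

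**What the plan says.** The collection rule for Cohort 1 appears twice in the protocol article, and the two statements agree. Data collection says of this cohort that "paper-based surveys will be collected by those who deliver the education program". Participants and recruitment methods has these clinical leaders complete the consent form, the Pre-test and Post-test 1 on the day and "return them to the researcher who is leading the education program".

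The surveys are described as de-identified, but they are coded with each participant's "initials and last three digits of their mobile telephone number". The timing is "Post-test 1: Immediately post the education program". Under Instruments, Post-test 1 holds the view-of-form item, the evidence-based-practice ratings, the relevance items on the teaching material, five items on the learning experience and, for Cohort 1, questions on readiness to teach others.

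The other routes differ. Cohort 2's forms from the day go to the researchers by registered post. Post-test 2 is completed online, and Strengths and limitations expects losses "when moving from paper based surveys to online surveys".

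**The concern.** The person receiving the form has a stake in what it says and can probably tell who wrote it. Each hospital has ten leaders, taught face to face for three hours, and the forms carry initials. The signed consent forms reach the same person on the same day. Under those conditions respondents may give kinder answers than they would in private, most plausibly on Post-test 1, which comes straight after the session and partly rates it.

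Two results are exposed in Cohort 1: the change from Pre-test to Post-test 1, and the Post-test 1 ratings of the program and of readiness to teach. Post-test 2 is not handed to the educator. A fall from Post-test 1 to Post-test 2 could therefore reflect the change of route and not a loss of learning. The study runs only in the five intervention hospitals and has no untaught comparison group in which a response shift would show itself. Strengths and limitations mentions recall bias and loss to follow-up, but not this.

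**Working it through.** **1. Collection conditions side by side**

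| | Cohort 1 | Cohort 2 |
|---|---|---|
| Teacher | Researcher leading the program | Cohort 1 clinical leaders |
| Pre-test | Paper, on the day, to the teacher | Paper, on the day, posted to researchers |
| Post-test 1 | Paper, on the day, to the teacher | Paper, on the day, posted to researchers |
| Post-test 2 | Online | Online |
| Consent form | Same day, same recipient | Same day, posted to researchers |

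The stated defect lies in Cohort 1. For Cohort 2 the article does not say who gathers the forms before posting, so exposure there is possible but not shown.

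**2. Does the bias cancel in the difference?** The Pre-test reaches the same person, so any general effect of being identifiable partly cancels. The Pre-test is completed before the teaching, however, so a wish to please the teacher should act mainly on Post-test 1 and remain in the difference.

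**3. The plan's own figure.** Data analysis gives α = 0.05, power 0.8, d = 0.4 and n = 50. Taking the test as two-sided (the article does not say) and paired:

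n = ((1.960 + 0.842) / 0.4)² = 49.1, rounded up to 50.

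The stated figure is reproduced. The exact paired t-test needs 52 and has power 0.792 at n = 50.

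**4. What a response shift would do.** The documents give no size for the bias, so the shift b is an assumption. Take no true change, two-sided α = 0.05, and a pure response shift of b standard deviations at Post-test 1.

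- Paired t, n = 50: noncentrality b√50, 49 df, with b in SDs of the within-person difference.
- Independent-samples t (the test the article names for two means), 50 per time point treated as independent: noncentrality b√25, 98 df, with b in SDs of the score.

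| Assumed shift b | Paired: chance of significance | Independent: chance of significance |
|---|---|---|
| 0 | 5% | 5% |
| 0.1 | 10.7% | 7.9% |
| 0.2 | 28.4% | 16.8% |
| 0.3 | 54.8% | 31.8% |
| 0.4 | 79.2% | 50.8% |

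For b = 0.2 the noncentralities are 0.2 × 7.07 = 1.41 and 0.2 × 5 = 1.00. The table shows how sensitive the Cohort 1 comparison is to a shift. It does not estimate the shift.

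**The case against.** Much can be said for the plan, and several stronger readings fail.

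- **That these forms supply every outcome.** A reader might infer this, but they do not. Cohort 2 is expected to be at least twice as large and also supplies survey outcomes. Confidential telephone interviews add qualitative data, though only from a few people at two sites.
- **That Cohort 2 is equally exposed.** Its forms are completed on the day it is taught by its own leaders, but they go to the researchers by registered post. Sight of the forms by those leaders is conjecture.
- **That change is inflated on all three primary outcomes.** The Outcomes section ties no survey item to any outcome. Behavioural change cannot be observed straight after a session and would have to rest on Post-test 2, which is online and repeats the Post-test 1 items. No pre-test value is described for readiness to teach, so there is no change to inflate; only the Post-test 1 rating is open to bias.
- **That the bias can be sized.** With an assumed item SD of 0.6 to 0.8, d = 0.4 is 0.24 to 0.32 points, which equals 24% to 32% of respondents moving up one category. Neither the SD nor the shading comes from the documents. In a paired calculation d is scaled by the SD of differences, which equals the item SD only if the correlation is 0.5. The conversion also does not fit the view-of-form item, a single choice from five statements.
- **That the collector causes all social desirability.** Some would remain whoever collected the forms. Only the part due to the collector is at issue.

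It is also fair to say that an article may leave envelope procedure to the full protocol, and that what participants are told may stand in the information and consent forms, which are not shown. Their absence here is no fault. What stands is the rule the article does state, twice, with the teacher as recipient.

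**Conclusion.** The point holds for Cohort 1. About 50 leaders hand recognisable forms to the person who taught them, straight after the teaching. This can add social-desirability bias to their change from Pre-test to Post-test 1 and to their Post-test 1 ratings of the program and of readiness to teach. It also makes collection conditions differ between Post-test 1 and Post-test 2.

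A shift in favour of the program is a reasoned expectation; the documents establish neither its direction nor its size. The rejection rates above rest on assumed shifts, no true change and a two-sided test. The change from Pre-test to Post-test 2 is less exposed, because it does not use Post-test 1. This is an inexpensive improvement to data collection. It does not invalidate the study or the Cohort 2 results.

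**What to change.** In Participants and recruitment methods and in Data collection, replace the Cohort 1 rule. State that participants seal their surveys in an envelope, separate from the consent form, and return them by drop box or by post to a researcher who does not teach. Add that the educator will not see individual answers. For Cohort 2, keep the registered post and add sealing beforehand, so that the clinical leaders who teach do not see the forms.

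The code that links a person's surveys can stay. The cost is envelopes, a box and a sentence in each section, with no extra visits. The educator can no longer check forms for completeness on the spot, and sealed return will reduce social-desirability bias without removing all of it.

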### Instruments

The ***Pre-test Survey*** identifies demographic characteristics of the sample such as profession, position, years of clinical practice experience, gender and location of work. It asks participants to select a single statement from a list of 5 to identify their view on the historical FRAT form and their view on what their colleagues might think. They are then asked to rate how strongly they agree or disagree on 20 statements regarding evidence-based practice falls risk assessment on a 5-point Likert scale from 1 (strongly disagree) to 5 (strongly agree). Free text comments are invited at the conclusion of the survey.

The ***Post-test 1 Survey*** repeats the 5-item statement to identify participants’ views on the forms. It also repeats 13 items from the pre-test survey on evidence-based practice and falls risk assessment with minor changes to 6 items and the addition of 4 new items (1 item is removed). Participants are asked to identify and comment on whether the new Falls Screening Tool will be beneficial to patients and to them personally. ***Post-test 1 Survey*** also includes 9 items from a previously validated Instructional Material Motivation Survey (IMMS) [22]. The relevance subscale from this survey is the only section to be used, as it has the most applicability and is an approach used in a previous thesis on falls prevention [23]. This section also includes 5 items seeking participants’ perceptions of the overall learning experience. Four open ended questions are included asking participants to comment on the effectiveness of the program such as what worked well, what needs improvement and their views on the ‘take home’ messages.

For Cohort 1, post-test survey 1 also asks participants additional questions around how prepared and confident they feel in educating others (Cohort 2) on this topic.

***Post-test 2 Survey*** repeats all items from Post-test 1 and makes minor changes to 3 items in the evidence-based practice and falls risk assessment section. Three open-ended questions are asked about the implementation of the new form along with whether the new form has been beneficial to patients and to them personally.

***Semi-structured telephone interviews*** (Additional file 3) will be conducted post implementation with consenting participants randomly selected from two randomly chosen experimental sites, in order to triangulate the data from the questionnaires and allow staff to state confidentially their thoughts on the changes to falls screening. Sequential explanatory design will be employed, where the qualitative data from the telephone interviews will help to explain or build on the initial quantitative results [24]. The quantitative phase will occur first using the surveys, and the qualitative component occurring subsequently via semi-structured telephone interviews, to gather detailed information about the education sessions and the new falls screening tools.

From Cohort 1, one health professional will be invited to participate. Cohort 2 interviewees invited to participate will consist of two other randomly selected staff - a junior staff member (qualified 3 years or less), and a senior staff member (qualified more than 3 years). Telephone Interviews will be audio-recorded for transcription purposes, and to ensure clarity and accuracy. See Table 1: Study Protocol.

**Table 1 Tab1:** Study protocol

Cohort 1	Cohort 2
Pre-test Characteristics of participants Views on historical FRAT form (*n* = 2 items) Views on EBP of falls (*n* = 20 items) Free text comments on falls screening and assessment	Pre-test Characteristics of participants Views on historical FRAT form (*n* = 2 items) Views on EBP of falls (*n* = 20 items) Free text comments on falls screening and assessment
3 h education program	1 h in-service
Post-test 1 Repeated items a/a (*n* = 13) Changed items (*n* = 6) Additional items (*n* = 4) 1 item removed IMMS Free text comments on falls assessment and the learning experience	Post-test 1 Repeated items a/a (*n* = 13) Changed items (*n* = 6) Additional items (*n* = 4) 1 item removed IMMS Free text comments on falls assessment and the learning experience
Post-test 2 Repeated items a/a (*n* = 13) Changed items (*n* = 6) Additional items (*n* = 4) 1 item removed IMMS Free text comments on falls assessment and the learning experience	Post-test 2 Repeated items a/a (*n* = 13) Changed items (*n* = 6) Additional items (*n* = 4) 1 item removed IMMS Free text comments on falls assessment and the learning experience
Individual Interviews	Individual interviews

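### The primary knowledge outcome is measured before and after only by strength of agreement, so a higher mean does not by itself show that knowledge increased

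*Protocol article*

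**What the plan says.** The Outcomes section of the Protocol article lists change in knowledge as primary outcome (ii). Under Instruments, pre-test participants "rate how strongly they agree or disagree on 20 statements regarding evidence-based practice falls risk assessment on a 5-point Likert scale", running "from 1 (strongly disagree) to 5 (strongly agree". Table 1 gives the same block the label "Views on EBP of falls (*n* = 20 items".

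The first aim, at the end of the Background, is to study the "self-reported views of hospital clinicians of their knowledge, clinical practice, confidence, motivation and attitudes towards screening for falls risk".

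Post-test 1 repeats 13 of the items, "with minor changes to 6 items and the addition of 4 new items (1 item is removed". Post-test 2 repeats the Post-test 1 items and makes small changes to three in this section. Data analysis describes the Likert responses and then tests for differences in mean scores across the three surveys. The article describes no test with right and wrong answers and no score reserved for knowledge.

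**The concern.** Knowledge and endorsement are different quantities. A knowledge measure counts whether an answer is correct. An agreement rating records how firmly a person holds a position, and its mean moves with firmness even when correctness does not change.

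The setting makes that distinction matter. Post-test 1 is completed straight after teaching on the evidence about falls screening and on implementing the new tool. Cohort 1 hands its forms to the person leading the session, and Cohort 2 is taught by its own clinical leaders. The education study runs only in the five intervention hospitals, so no untaught group shows how far ratings move without learning.

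At stake is the meaning of a primary outcome. A significant rise in mean agreement would be filed under change in knowledge, and the abstract presents the study as quantifying a program meant to increase knowledge. The instrument as described supports a narrower statement: that clinicians' self-reported views changed.

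**Working it through.** **1. The plan's own figure.** Data analysis gives n = 50 for α = 0.05, power 0.8 and d = 0.4. Taken as a two-sided paired comparison (an assumption, since the article states neither feature), n = ((1.9600 + 0.8416) / 0.4)² = 7.004² = 49.06, rounded up to 50. The figure reproduces to the normal approximation. It does not bear on this point, because d = 0.4 is not attached to any named score and so does not show what would count as knowledge.

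**2. Which components could carry outcome (ii)?** It needs a pre-test value, a post-test value and a link to knowledge.

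| Component (Instruments) | Pre-test value? | What it records |
|---|---|---|
| Two single-choice items on the historical form | Yes | Own view and presumed view of colleagues |
| 20 agreement items | Yes | Strength of agreement, labelled views |
| IMMS relevance subscale: the first post-test "also includes 9 items from a previously validated Instructional Material Motivation Survey (IMMS) [22" | No | Relevance of the material |
| Cohort 1 only: "additional questions around how prepared and confident they feel in educating others (Cohort 2) on this topic" | No | Preparedness and confidence to teach |
| Learning-experience items | No | Perception of the session |
| Free text and interviews | Not quantitative (interviews only after implementation) | Explanation of the survey results |

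Only the agreement items remain.

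**3. Item counts.** Pre-test: 13 repeated + 6 changed + 1 removed = 20. Post-test 1: 13 + 6 + 4 new = 23. At Post-test 2, three items are altered. The text does not say which, so between 13 − 3 = 10 and 13 items have identical wording at all three surveys.

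**4. What a mean rating can and cannot show.** For one item, let p_r be the share choosing rating r. The mean is Σ r·p_r. If the statement is true, the share correct is p_4 + p_5.

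- A fraction f moves from 4 to 5: the mean changes by f × (5 − 4) = f, and the share correct changes by 0. With f = 0.5 as an illustration, the mean rises by 0.5 and no answer is newly correct.
- A fraction g moves from 3 to 4 out of acquiescence: the mean rises by g, and the share correct also rises by g. Keying removes the first problem but not this one.
- If a statement is false, learning lowers its mean. Without a stated key, even the direction of a change in the mean has no fixed meaning. Whether any item is worded this way is not shown.

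Averaging over items averages these shifts, so the argument holds for item-by-item means and for a pooled mean.

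**The case against.** The strongest reply is that the item wording is not shown. Some statements may be factual, and a key or reverse scoring may sit in the questionnaire or the full protocol, which a journal article need not reproduce. The article is also open about self-report: aim (i) says so, Table 1 prints the label, the limitations mention inaccurate self-reporting, and interviews are used for triangulation. Post-test 2 comes two months after implementation, when the pressure of the session has faded.

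Part of this stands. The absence of a scoring key from the article is not the fault. The fault lies in what the article does fix: a knowledge outcome, an agreement response format labelled views, and a comparison of means. The stated limitation concerns recall bias, which is a different problem. The interviews are qualitative and have no baseline. Post-test 2 uses the same agreement format.

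Three stronger readings are tempting, and the document does not support them.

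- A reader might infer that the 20 items mix knowledge, practice, confidence, motivation and attitudes. Aim (i) lists all five but does not assign them to these items, and other components partly serve some of them.
- A reader might infer one pooled score that non-knowledge items could push to d = 0.4. The article speaks only of mean scores, which may be per item. Any size is also guesswork. With 4 to 16 of 20 items assumed non-knowledge, each rising 0.25 to 1.0 point, and an SD of 0.5 to 1.0, d runs from (4 × 0.25 / 20) / 1.0 = 0.05 to (16 × 1.0 / 20) / 0.5 = 1.6.
- A reader might infer that the trial will announce a false knowledge gain. The sentence in Data analysis on a statistically significant intervention effect concerns conceptual change to the new form.

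**Conclusion.** The concern holds as a mismatch between a named primary outcome and the only measure described for it. A rise in mean agreement, however scored, does not by itself support a conclusion that knowledge increased. This follows from the stated response format, label and analysis, and needs no assumption about item content.

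No numerical size can be attached, because the item wording and the standard deviation are not given. The consequence is for the wording and strength of one primary conclusion. The data remain usable for what they record, namely self-reported views. Because the correction is cheap and changes what the trial can conclude, it should be made before the data are analysed.

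**What to change.** Restate primary outcome (ii), and any conclusion drawn from it, as change in self-reported views (perceived knowledge) of evidence-based falls screening.

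If some items whose wording is identical at the surveys being compared have a factual answer supported by the taught evidence, then before analysis:

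- name those items and key the correct direction of each;
- report per cent correct on those items alone as the knowledge result;
- report the remaining items separately, as self-rated views.

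The cost is a change of outcome wording and, if the second route is used, a short scoring key. No new data are needed. The downside is either a weaker claim or a knowledge score that rests on fewer, dichotomised items. Keyed agreement items still do not fully exclude acquiescence, and the report should say so.
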